### Outcome measures and subject’s characteristics

#### Primary outcome

The primary outcome is the score on the Japanese version of the SI-R. The SI-R score is an index used to gauge the difficulties posed by a hoarding disorder (a higher score indicates a greater tendency to hoard). It measures mental anguish caused by hoarding and the impacts of hoarding on life. A higher score indicates a greater tendency to hoard.^2 21^ There is presently no Japanese version of the Child Saving Inventory.^25^ The academic ability of Japanese teenagers, however, ranks among the top in the world.^26^ Only 292 Japanese *kanji* characters are used for the Japanese version of the SI-R, and most have already been learnt in elementary school. Therefore, the Japanese version of the SI-R is applicable for junior high school students and should not create problems related to comprehension.

The primary effect size is the difference changes in SI-R score from baseline to 7 months between the two groups. The hypothesis of this study is that the mean SI-R score of the intervention group will decrease more than that of the control group.

#### Secondary outcomes

Secondary outcomes include:Score on the Clutter Image Rating (CIR) Scale, which measures clutter using photographs of rooms (a higher score indicates more clutter).^27 28^
Score on the Japanese version of the Rosenberg Self-Esteem Scale.^29^ This measures the degree of self-respect and the value placed on the self. A high score shows stronger feelings of self-esteem.Score on the Roles of Private Space Scale. This linear measure observes the function, the necessity and securement level of private space.^30^

These outcomes will be used to examine the amount of decluttering and organising, including frequency of cleaning and number of visitors in a week. They will allow the researchers to assess the state of subjects’ living spaces and their ability to declutter and organise because of the workshop.

#### Subject characteristics

During the first meeting, participants will provide information about their gender, age, comorbidities, previous history, medication, number of roommates/family members in their household, number and size of living spaces, how often their living space is organised and tidied up, number of visitors to their living space in the previous week, whether they have difficulty decluttering and organising and are living with a roommate or family members and aspects of social status such as occupation, marital status, educational background and work pattern (whether they are working on a shift basis).

### Statistical analysis

#### Sample size

A previous study divided 46 patients with a hoarding disorder (mean age: 53.9 years) into two groups. One group of 23 subjects was scheduled for 26 sessions of cognitive–behavioural therapy approximately on a weekly basis. The second group of 23 subjects had yet to undergo cognitive–behavioural therapy.^19^ A comparison of the two groups indicated that subjects who had completed the 12th session of cognitive–behavioural therapy had a 10-point drop in their SI-R score. Around 10 points were improved on using a pre-test on the general population. A meta-analysis in another study indicated that intervention was more effective in younger individuals than older ones. This study therefore assumed a potential 10-point improvement in SI-R score.^19^ Previous results indicated that the SI-R score had a normal distribution and SD was 13.0.^20^ The sample size was therefore calculated as 28 per group under the assumptions of a significance level of 5% (two tailed), a power of 80% and an effect size of 0.75. Considering the likely dropout rate, we set the sample size needed for this trial as 60 subjects in total, 30 in each group.

#### Statistical analysis

Analyses will be conducted under the intention-to-treat principle. The main target set for analysis is the full analysis set. Missing data will be permutated under the assumption of missing at random following the last observation carried forward principle. A sensitivity analysis will be performed using the multiple imputation method. The secondary target set for the analyses will be the per-protocol set.

Summary statistics (maximum, median, minimum, mean and SD) will be calculated for all continuous data, and frequency and proportion for categorical data.

The differences in effect sizes between the two groups will be examined using a t-test. Differences will be assessed in a general linear model by adjusting for gender, age and marital status at the start of the study and outcome measure at the baseline. Crude and adjusted ORs will be calculated for binary variables and the two groups will be compared using logistic regression analysis. As secondary analysis, mixed-effects random-effects models will be used as a longitudinal data analysis. The significance level for testing will be set at p<0.05 (two tailed).

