#### Control group

The control group will receive an initial inspection to evaluate room cleanliness or clutter once eligibility is verified and consent obtained. The second inspection will take place before the intervention group starts the workshop. The control group will receive a visit from a professional cleaning company only to declutter the living spaces. Further inspections will take place 4 weeks, 2 months, 4 months and 7 months after the start of the study. Members of the control group who wish to attend the workshop may do so after the study period ends.

Additionally, until the end of the research period 7 months after commencement of the study, no participants are allowed to directly request any cleaning service be done.

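### The primary analysis fills missing SI-R scores by last observation carried forward and justifies this by missing at random, an assumption under which the method is not valid

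*Protocol article*

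**What the plan says.** All of the following is in the protocol article.

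- **Endpoint** (Primary outcome): "The primary effect size is the difference changes in SI-R score from baseline to 7 months between the two groups".
- **Analysis set** (Statistical analysis): "The main target set for analysis is the full analysis set", under intention to treat.
- **Test** (Statistical analysis): "The differences in effect sizes between the two groups will be examined using a t-test", followed by a general linear model adjusted for gender, age, marital status and the baseline value.
- **Missing data** (Statistical analysis): "Missing data will be permutated under the assumption of missing at random following the last observation carried forward principle". I read the verb as a slip for imputed and make nothing of it.
- **Other methods** (Statistical analysis): "A sensitivity analysis will be performed using the multiple imputation method", and "As secondary analysis, mixed-effects random-effects models will be used as a longitudinal data analysis".

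LOCF is thus the only rule given for the main result. Multiple imputation and the mixed model have supporting roles.

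**The concern.** Under missing at random, a dropout's unseen later score can be predicted from what was observed. That prediction may well be further improvement or a relapse. LOCF allows neither: it sets the later score equal to the last one. Missing at random does not imply this, so the stated justification does not support the stated method.

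A frozen score also sits badly with the plan's own reasoning. The Subject assignment section defends the 7-month term on the ground that education about habits takes months to show its effect. Scores are therefore expected to keep moving after the early contacts. Both arms also receive a cleaning visit, so an early gain that later fades is equally conceivable.

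Unequal dropout is plausible. The trial is open label, only one arm is asked to attend four two-hour sessions, and outcomes come from surveys that participants send in themselves. At stake is the headline 7-month difference. The two supporting analyses could reveal a distortion but would not repair that estimate.

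**Working it through.** **1. The plan's own figures.** The Sample size section gives a standardised effect of 0.75, two-sided 5% and 80% power. It rests on this: "This study therefore assumed a potential 10-point improvement in SI-R score", with SD 13.0. The normal approximation gives n = 2 × (1.96 + 0.842)² / 0.75² = 27.9, so 28 per group, which matches (an exact t-test gives 29). The article states no dropout rate, but 28 raised to 30 implies 1 − 28/30 = 6.7%.

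**2. Bias formula.** Let d be the dropout proportion in an arm. Let r be the mean later movement that LOCF misses (7-month score minus last recorded score; positive for a rebound, negative for a further fall). The bias in the apparent workshop benefit is

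d_I × r_I − d_C × r_C.

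**3. Equal dropout of 6.7%, true difference 10.** I assume that dropouts would have followed their arm's mean, with changes of −15 (workshop) and −5 (control).

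- Baseline carried forward: 0.0667 × (−15) − 0.0667 × (−5) = −0.67, so 9.33 is estimated.
- Half the change already reached: 0.0667 × (−7.5) − 0.0667 × (−2.5) = −0.33, so 9.67.
- Equal rebound in both arms: the terms cancel and the bias is 0.

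**4. Unequal dropout, assumed 20% workshop v 7% control.**

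- 5-point rebound in both arms: 0.20 × 5 − 0.07 × 5 = +0.65, a false benefit.
- 8-point rebound: 0.20 × 8 − 0.07 × 8 = +1.04.
- Further fall of 5 points in both arms: 0.20 × (−5) − 0.07 × (−5) = −0.65, a false harm.

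The planned standard error is 13 × √(2/30) = 3.36, so 0.65 to 1.04 points is about 0.2 to 0.3 of it.

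**5. Simulation under missing at random.** 20,000 trials; 30 per arm; scores at 0, 1, 2, 4 and 7 months; SD 13; correlation 0.5; scores falling steadily; the chance of leaving rises with the latest observed score. Trajectories, correlation and dropout are all assumptions.

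| True difference | Dropout, workshop v control | LOCF estimate | Rejection rate |
|---|---|---|---|
| 10 | 8% v 8% | 9.43 | 0.78 |
| 10 | 23% v 23% | 8.54 | 0.69 |
| 10 | 33% v 12% | 6.35 | 0.44 |
| 10 | 12% v 33% | 10.72 | 0.88 |
| 0 | 23% v 23% | 0.0 | 0.052 |
| 0 | 16% v 0% | −1.6 | 0.077 |
| 0 | 33% v 12% | −2.2 | 0.098 |

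With complete data the rejection rate was about 0.83 for a true difference of 10 and 0.05 for none. Some of the power loss reflects lost data, which any method would suffer. Multiple imputation and the mixed model were not simulated.

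**6. Standard error.** LOCF counts all 30 per arm as observed. With 28 observed, the completers' standard error is larger by √(30/28) = 1.035, about 3.5%. In the simulation with 23% missing, the LOCF value was 3.40, against 3.34 × √(1/0.771) = 3.80 for completers.

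**The case against.** Several points on the other side stand.

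- **The plan is not without a method suited to missing at random.** It prespecifies both multiple imputation and a longitudinal mixed model, so a distortion would probably be seen.
- **The size is modest on the only dropout information given.** At 6.7% in both arms the loss is under a point, and it can be zero. The 20% v 7% case, and still more the 33% v 12% case, have no basis in the article.
- **Interim SI-R scores are not certain.** The Control group section says: "Further inspections will take place 4 weeks, 2 months, 4 months and 7 months after the start of the study". These are room inspections, and the Intervention group section gives the same times. The Primary outcome section names only baseline and 7 months for the SI-R. Surveys sent together with room photographs, and the planned longitudinal model, make interim scores likely, but no section fixes them. Without them the rebound figures do not apply and LOCF becomes baseline carried forward, unless the full analysis set leaves out participants without follow-up.

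A reader might also infer that the result is wrong whenever anyone drops out, or that the confidence interval is seriously too narrow. Neither is supported. With equal dropout, the same trajectories and no true effect, LOCF gave no bias and a type I error of 0.052. In the simulation its standard error matched the sampling variation of the LOCF estimate itself. The fault is that it understates uncertainty about the 7-month effect, and at 6.7% dropout this is slight.

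None of this rescues the justification. The article fixes the method and gives it a reason that does not fit, so this is not a detail left to an analysis plan.

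**Conclusion.** The point holds in a limited form. The primary rule for missing SI-R data claims missing at random and then uses a method that needs frozen scores. The size depends on dropout:

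- **Equal dropout at the implied 6.7%:** about 0.3 to 0.7 of 10 points lost towards no effect, assuming dropouts would have followed their arm's mean and had reached between none and half of their change. The standard error is understated by at most about 3.5% relative to completers.
- **Unequal dropout (assumed 20% v 7%, rebound of 5 to 8 points, interim SI-R collected):** a false difference of about 0.65 to 1.0 points.

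The direction cannot be known in advance. A reader might take LOCF to be conservative here, or to favour the workshop. The documents support neither, because the sign turns on whether scores are still falling or rebounding and on which arm loses more participants.

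**What to change.** - Make the planned multiple imputation, feeding the baseline-adjusted general linear model, the primary analysis of the 7-month change. The imputation model should include arm, baseline SI-R, the listed covariates and any interim SI-R scores.
- If SI-R is collected at the interim times, the 7-month contrast from the planned mixed model is an equally acceptable primary analysis. Choose one and say so, and state the SI-R collection times.
- Demote LOCF to a sensitivity analysis or delete it, and remove the statement that it rests on missing at random.
- Make the change by a dated amendment before outcomes are compared by arm. The Timeframe of the study section describes data collection as still under way, so this was possible when the article was written.

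The cost is a slightly wider confidence interval and a little more analysis work. Sample size and data collection do not change.

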### Timeframe of the study

Participants were registered between January and May 2016. Eight workshops have been run between 3 February and 11 June 2016. Data are currently being collected.

### Data management

Personal information obtained in this study will be coded. Participant files will be stored in numerical order in a secure but accessible place and manner. Data will be anonymised before analysis. Data will be kept on a password-protected computer with limited access.

The study organiser will keep all documents related to this trial in a locked cabinet. Five years after the study is presented, or 3 years after the final publication of the results (whichever is later), all documents will be disposed of using a document destruction service contracted by the University.

### Conditions for discontinuation of this study and actions in that event

When significant information about the safety or effectiveness of the intervention is obtained, the study organiser will determine whether to continue the study.

### Treatment of subjects after this study is conducted

If the intervention group is performing significantly better than the control group at the end of the study, the control group will be informed. Members of the control group who wish to do so may then attend the workshop after the conclusion of this study.

### Monitoring

Information on when the study begins, the conduct of the study (sample size), ethical considerations that have been made, the occurrence of any detrimental or adverse events, the results of the study and registration of the study with a public database will be submitted to the ethics committee in an annual interim report. A report will also be submitted to the ethics committee on the conclusion of the study and when the final results are presented.

### Protocol amendments

If any occur, the ethics committee may be notified as necessary.

### Follow-up of adverse events

This study involves attending a workshop programme to help people declutter and organise and receiving visits from a professional organising and cleaning service. There is little likelihood of any health hazards to the subjects. If any serious adverse events occur, they will be reported in line with the standard operating procedure on Reporting Serious Adverse Events in Clinical Research.

### Ethics and dissemination

The Medical Ethical Committee of Teikyo University (No. 15-065) has approved the study protocol. The findings will be disseminated widely through peer-reviewed publication and conference presentations.

Study participant candidates will be given an explanation form. The study will be fully explained orally and in writing, and voluntary consent for study participation will be sought in writing. The explanation and consent form is shown in online supplementary files 1–8. Considerations have been made in the event a participant consents to take part but later withdraws that consent. Participants will be assured they will not be penalised for withdrawal or for not participating. Participants will be informed of the study’s results after its conclusion and on their request. Those aged 12–14 years must provide written informed assent together with an adult consent form from the parents. Those aged 15–18 years must provide written consent (same as for adults) and a guardian consent form. The ages for requisite informed assent were decided with reference to the guidelines of the American Academy of Pediatrics^31 32^ and the decision of the Teikyo University Ethics Committee. Minors living with a guardian or family member (in this section hereinafter ‘relevant party’) will have a similar form mailed to the relevant party or the minor will be asked to deliver it to the relevant party. If information is obtained that may affect the participant or the relevant party, or if the protocol is modified to such an extent that the change would affect the consent of all relevant parties, that information will be promptly provided to the relevant parties and the participant’s desire to continue will be verified. In either of the aforementioned instances, the Research Ethics Committee will revise and approve the consent and explanation form, and the consent of all relevant parties will be sought.

Participants who wish to view their information or withdraw consent may contact the study chair for resolution. Any modifications to the protocol that may affect the conduct of the study will be presented to the aforementioned committee.

## Discussion

One aim of this study is to assess the effect of an intervention (a workshop) on the state of living spaces and the quality of life of younger people who have difficulty decluttering and organising and who therefore have a cluttered living space. If the approach is found to be effective, then the findings of this study will be widely publicised and the workshop materials will be made widely available, so that it can be conducted by others, including administrative bodies and professional organisers and cleaners. This should improve the quality of life and help to prevent a hoarding disorder in younger people who have difficulty decluttering and organising.

This study has certain strengths and weaknesses. Blinding is not possible because of the type of intervention. It is impossible to create a convincing placebo for the workshop on decluttering and organising, and this lack of blinding may affect the results. As far as possible, subjects need to have an experience equivalent to undergoing training from a professional organising and cleaning service.

10.1136/bmjopen-2016-014687.supp1Supplementary material 1

10.1136/bmjopen-2016-014687.supp2Supplementary material 2

10.1136/bmjopen-2016-014687.supp3Supplementary material 3

10.1136/bmjopen-2016-014687.supp4Supplementary material 4

10.1136/bmjopen-2016-014687.supp5Supplementary material 5

10.1136/bmjopen-2016-014687.supp6Supplementary material 6

10.1136/bmjopen-2016-014687.supp7Supplementary material 7

10.1136/bmjopen-2016-014687.supp8Supplementary material 8
